**Figure 1 FIG1:**
[figure not shown]
A depiction of the PsilOCD study timeline: the total period from the first preparation session (Prep. 1) to the final integration session (Int. 4). EEG: Electroencephalography; ECG: Electrocardiogram; MINI: Mini-International Neuropsychiatric Interview

Preparation

Preparatory sessions serve to initiate the self-reflective therapeutic process, build trust and rapport with the therapists, remind participants of what to expect from the dosing days, and start discussing themes that arise for them related to their OCD symptoms. Any changes in participants’ symptoms, well-being and attitude towards the study are documented. Preparatory sessions occur one week and one day before each Dosing Day.

Dosing Day 1 and 2

The participant will arrive at the clinic (Central and North West London (CNWL)-Imperial Psychopharmacology & Psychedelic Research (CIPPRes) Clinic, at CNWL NHS Trust’s St Charles Hospital) in the morning, and will be administered psilocybin (1 mg on the first visit and 10 mg on the second). The therapists will offer non-directive psychological support throughout the dosing days. One hour after the substance wears off, the EEG vLTP paradigm will be carried out to quantify enhancements in plasticity. Bloods will be taken and tested for BDNF levels, as well as immune markers. The participant’s subjective experience will also be assessed using questionnaires (the Mystical Experience Questionnaire (MEQ), the Challenging Experience Questionnaire (CEQ) and the Emotional Breakthrough Inventory (EBI)), and they will be prompted to estimate the dose of psilocybin that they received. This day will end at approximately 17:30, at which point they will be driven home in a taxi or collected by a trusted contact.

Integration

The participant will attend three integration sessions with the therapists, designed to help them interpret any insights and apply them to their lives. These sessions will take place one day, one week and two weeks after each dosing day. The Y-BOCS will also be conducted again, as well as the aforementioned measures of affective symptoms.

Neuropsychological Task Performance (CANTAB Test Battery)

Study collaborators from the University of Cambridge will administer the CANTAB test battery remotely two days after each dosing session. This will involve ED-shift outcome measures using ID-ED Set Shift, Probabilistic Reversal Learning, and Paired Associates Learning task (a neutral control task).

One-Month Follow-ups

These two remote sessions will take place one month after each dosing session. The first will mainly be a preparation for the second dose, taking place one day before the second dosing day; the second follow-up will be a final psychological integration session, and a discussion of the participant’s experience partaking in the study. The Y-BOCS and affective symptoms tests will also be conducted a final time.

Low-moderate dose psilocybin administration with psychotherapeutic support

While PsilOCD is primarily a pharmacological challenge study, safely administering this drug in clinical populations requires psychotherapeutic attunement and support [74]. There is currently no standardised protocol for this intervention, but common principles shared across studies will be applied in this investigation such as intention setting, offering psychoeducation about navigating psychedelic experiences, and other non-directive and positive humanistic approaches [75]. Even though most of the literature concerning psilocybin treatment involved higher doses of psilocybin than PsilOCD, this trial's psychotherapeutic model is inspired by it and aims to facilitate a compassionate, self-guided psychological journey [76].

To maintain consistent conditions, participants will receive the same therapeutic support before, after and during both dosing sessions. Participants will attend study sessions in a comfortable, softly lit setting, where they will be encouraged to recline and wear eye masks. Recognising the influence of music on emotional states and potentially therapeutic outcomes during the dosing sessions, playlists have been curated by experienced researchers in the field of psychedelics [77]. Participants will stay introspective during the effects of the drug experience to maximise the non-directive approach and be sensitive to opportunities for psychological change [78]. While the psychotherapeutic container is mostly non-verbal on dosing days, the therapists will ask participants to rate the intensity of the psilocybin every 40 minutes.

Since PsilOCD is a feasibility study designed to pave the way for future research into OCD and psychedelics, no OCD-specific therapy is administered. This will permit the lucid assessment of the pharmacological effects of psilocybin when paired with encouraging, but non-interventional, therapeutic support.

Throughout the study, each participant will be supported by two guides. These guides will assist with the entire process, beginning with virtual preparation sessions to help participants understand and get ready for the experience. During each dosing session, the guides will accompany participants in a private room and will follow up with four integration sessions after each dose. Dosing sessions are scheduled for the day after the second preparation meeting. Each participant will spend roughly nine hours at the research facility, with the drug effects expected to last between four and six hours. While participants are encouraged to use eye masks and headphones, this is optional. EEG recordings will be conducted both before and during the peak drug phase. An on-site medical professional will oversee participant safety throughout, giving approval before participants leave the facility. Those living locally may return home if accompanied by a trusted person, while others are provided with overnight accommodation at the facility.

The first integration session is conducted the morning after the dosing day, allowing participants to meet virtually with their guides to discuss their psilocybin experience. All themes that arise, whether related to OCD or not, will be further examined in the integration sessions held over the four-week follow-up period following each dosing day.

Safety, monitoring, and reporting procedures

Maintaining the safety of participants is the paramount guiding principle that informs all decisions related to the study. Participants will be continuously accompanied by a member of our research team on dosing days, and their departure will be subject to the on-site physician's evaluation of their safety. Additionally, the well-being of participants will be assessed by their two therapists the morning following dosing and in all subsequent integration sessions. Participants will be informed that the study psychiatrist is available 24/7 for emergency calls, should anything untoward occur.

Outcome measures

See Table 2 below for the study outcome measures. These comprise neurophysiological, psychiatric, self-reported, and cognitive metrics.

**Table 2 TAB2:** Summary of PsilOCD Outcome Measures and Hypotheses ID: Intradimensional; ED: Extradimensional; CANTAB: Cambridge Neuropsychological Test Automated Battery; EEG: Electroencephalography; vLTP: Visual long-term potentiation; Y-BOCS: Yale-Brown Obsessive Compulsive Scale; MADRS: Montgomery-Asberg Depression Rating Scale; PROM: Patient-reported outcome measure; BDNF: Brain-derived neurotrophic factor

Outcome Type	Outcome Measure	Hypothesis
Primary Clinical Outcome	Cognitive Flexibility: ID-ED Shifting (CANTAB)	Participants will show improved scores on the CANTAB ID-ED task two days after the 10 mg psilocybin dose compared to two days after the 1 mg dose.
Primary Neuroimaging Outcome	Neuroplasticity: EEG vLTP	Participants will demonstrate higher capacity for neural plasticity two hours post 10 mg dose compared to the 1 mg dose, as indicated by vLTP in EEG recordings.
Secondary Clinical Outcome	Y-BOCS and MADRS Scores	Y-BOCS scores for obsessions and compulsions are expected to decrease after the 10 mg dose but not after the 1 mg dose. MADRS scores will likely follow a similar pattern.
Secondary Clinical Outcome	Cognitive Inflexibility: Reversal Learning (CANTAB)	Participants will show improved scores in reversal learning two days post 10 mg psilocybin dose, but not two days post 1 mg dose.
Secondary Clinical Outcome	Cognitive Inflexibility: Paired Associates Task (CANTAB, Control Task)	Scores are expected to be comparable after both 1 mg and 10 mg doses, as visuospatial tasks should not be affected by 5-HT2A receptor modulation.
Secondary Clinical Outcome	Cognitive Inflexibility: Information-Seeking Task	If psilocybin reduces the rigidity of high-level priors, confidence will improve, and information-seeking behavior will reduce. Significant effects are expected one day after the 10 mg dose, not the 1 mg dose.
Secondary Clinical Outcome	Self-Reported Well-Being and Affective Measures (PROMs)	Compared to 1 mg, the 10 mg dose is expected to improve anxiety and depression-related symptoms, decrease impulsivity (Barratt Impulsivity Scale), increase openness, and decrease neuroticism (Big Five Inventory).
Secondary Clinical Outcome	Acute Subjective Experiential Measures (PROMs)	The 10 mg psilocybin dose will result in significantly higher scores on questionnaires assessing subjective drug effects compared to the 1 mg dose.
Secondary Clinical Outcome	Blood Analysis: Serum BDNF and Plasma Inflammatory Markers	The 10 mg dose, but not the 1 mg dose, will significantly increase serum BDNF levels and reduce plasma markers of inflammation. This outcome is exploratory and focuses on psilocybin's potential acute anti-inflammatory effects.

Mechanistic neurophysiology outcome measures

In order to ascertain the effect of this low dose of psilocybin on neuroplasticity in an OCD population, the vLTP EEG paradigm will be run at three time points during the course of the study. The first EEG session takes place during the in-person screening day to acquire baseline recordings, while the subsequent two are done on both dosing days after the effects of the drug have worn off (two hours after dosing).

The vLTP paradigm uses tetanising visual stimulation to measure the brain's capacity to undergo neuronal plasticity, specifically in the occipital lobe where we can easily measure evoked responses to external visual stimuli. This vLTP paradigm was developed at the University of Auckland and is now incorporated into several psychedelic trials both at the University of Auckland and Imperial College London. As the vLTP paradigm quantifies neuroplasticity, this will provide valuable insight into whether psilocybin enhances it in OCD patients.

Cognitive tasks

As cognitive inflexibility is a hallmark characteristic of OCD and potentially causal to the onset of symptoms, we are investigating it through several cognitive tasks. The first, the ID-ED task, is delivered as part of the CANTAB; it measures participants’ ability to switch their focus from one dimension of a task (set of stimuli) to another. The reversal-learning task, also part of the CANTAB, assesses their ability to learn to no longer apply a rule when it becomes obsolete. The final CANTAB task, the visuospatial paired-associates task, serves as a control and will indicate the order effect at play. Scores are not expected to be influenced by psilocybin. The information-seeking task developed by Schulz et al. measures participants’ tendency to seek extra information, assessing confidence and decision-making [79].

Patient-reported outcome measures

While the primary interest of the study is in the neural mechanisms involved in psychedelic-mediated action in an OCD population, we will also collect efficacy measures at every time point of the study. PROMs will be collected remotely via the online survey platform ‘Qualtrics’, with groupings of questionnaires corresponding to different study visits. All baseline self-reported measures will be taken at the second preparatory session (Visit 3), except for PROMs designed to test participants’ perception of the psilocybin experiences (these baseline measures shall be taken on the first dosing day). Baseline EEG will be collected at the screening visit. Please see Table 3 below for a full list of PROMs. PROMs are grouped as ‘Obsessionality-Related Outcomes,’ ‘Affective Outcomes,’ and ‘Acute Subjective Psilocybin Measures’. We will also collect ‘Patient Impression Measures’ to assess the effects of expectancy and blinding efficacy. We hypothesise improvements in Obsessionality-Related Outcomes and Well-Being/Affective Outcomes.

**Table 3 TAB3:** PsilOCD outcome measures DFU: Day follow-up (e.g., 1DFU1 = first one-day follow-up); CANTAB: Cambridge Neuropsychological Test Automated Battery; WFU: Week follow-up; MFU: Month follow-up; EEG: Electroencephalography; vLTP: Visual long-term potentiation; MMN: Mismatch negativity; Y-BOCS: Yale-Brown Obsessive Compulsive Scale; MADRS: Montgomery-Asberg Depression Rating Scale; ID: Intradimensional; ED: Extradimensional; BDNF: Brain-derived neurotrophic factor; PROM: Patient-reported outcome measure; WBSI: White Bear Suppression Index; CPAS: Compulsive Personality Assessment Scale; CAIOC: The Cognitive Assessment Instrument of Obsessions and Compulsions; PHQ: Participant Health Questionnaire; BDI: Beck's Depression Inventory; SDS: Sheehan Disability Scale; STAI S/T: The State/Trait Anxiety Inventory; BSL: Borderline Symptom List; BIS: Barratt Impulsiveness Scale; bEAQ: Brief Experiential Avoidance Questionnaire; PID-5-FBF: The Personality Inventory for DSM-5 (Faceted Brief Form); MEQ: Mystical Experience Questionnaire; CEQ: Challenging Experience Questionnaire; EBI: Emotional Breakthrough Inventory; GEMS: Geneva Emotional Music Scale; PMQ: Psychedelic Music Questionnaire; PIS: Psychological Insight Scale Xa: Assessment only after pharma-challenge (or prep); Xb: Assessment only before pharma-challenge/prep; Xab: Assessment before and after pharma-challenge/prep

Visit #			-	V1	V2	V3	V4		V5		V6	V7	V8	V9	V10	V11	V12	V13	V14	V15
Visit Name			Video Screening	In-Person Screening	Prep 1	Prep 2	Dose 1		1DFU1		CANTAB	1WFU1	2WFU1	1MFU1 / Prep-3	Dose 2	1DFU2	CANTAB	1WFU2	2WFU2	1MFU2
Day			At least 2W from V4	At least 2W from V4	D-1 (>1W pre V4)	D-7 (>1D pre V4)	D-8		D-9		D-10	D-15	D-22	D-34	D-42	D-43	D-44	D-49	D-56	D-70
Face-to-Face				X			X								X					
Virtual (Microsoft Teams)					X	X			X		X	X	X	X		X	X	X	X	X
Dosing Days							X								X					
EEG																				
Resting State (Eyes Closed)				X			X								X					
Resting State (Eyes Open)				X			X								X					
vLTP				X			X								X					
MMN				X			X								X					
Clinician-Rated Scales																				
Y-BOCS			X			X						X	X	X				X	X	X
MADRS			X			X						X	X	X				X	X	X
Cognitive Tasks																				
ID-ED Set-Shifting Task											X						X			
Reversal Learning Task											X						X			
Paired-Associates Task											X						X			
Information-Seeking Task											X						X			
Physiological Measures																				
Oura Ring (Data Collected Throughout study)				X	X	X	X		X		X	X	X	X	X	X	X	X	X	X
Blood Analysis																				
BDNF (Plasma Levels)							X								X					
Epigenetic Markers (Plasma Levels)							X								X					
Immune Markers (Plasma Levels)							X								X					
PROMs																				
Obsessionality-Related Outcomes																				
Challenge Y-BOCS							Xba		X						Xba	X				
WBSI					X									X						X
CPAS					X															
CAIOC-13					X									X						X
Affective Outcomes																				
PHQ					X	Xb	(Xb)					X	X	X	(Xb)			X	X	X
BDI						Xb							X	X					X	X
SDS					X							X	X	X				X	X	X
STAI T					X	Xb	(Xb)					X	X	X	(Xb)			X	X	X
STAI S							Xba		X						Xba	X				
BSL-23				X																
BIS					X									X						X
bEAQ					X									X						X
Hybrid Personality Measure					X									X						X
PID-5-FBF					X									X						X
Breaking of Blind Question							Xa								Xa					
Menstrual Cycle-Related Questions (Female Participants)				X	X	X			X			X	X	X		X		X	X	X
Premenstrual Symptoms Screening Tool (Female Participants)				X	X	X			X			X	X	X		X		X	X	X
Acute Subjective Psilocybin Measures																				
Acute State Scales (MEQ, CEQ, EBI)							Xa								Xa					
GEMS, PMQ							Xa								Xa					
PIS									X			X				X		X		

Peripheral physiological data

Physiological data including heart rate variability (HRV), actigraphy, and sleep staging will be collected using Oura Ring devices throughout the study.

Bloods

The blood biomarkers to be assessed in this study will be measured from samples collected at two time points: 30 minutes before and two hours after the end of each psilocybin dosing session. A key biomarker to be assessed is BDNF, primarily linked to neuroplasticity-related processes including synaptogenesis.

A range of markers implicated in the immune response will also be explored, including interleukin-1 receptor antagonist (IL-1RA), C-reactive protein (CRP), insulin-like growth factor 1 (IGF-1), mucosal vascular addressin cell adhesion molecule 1 (MadCAM-1), intestinal fatty acid-binding protein (I-FABP), lipopolysaccharide-binding protein (LBP), and C-C motif chemokine ligand 25 (CCL25), B-cell activating factor (BAFF), and S100 calcium-binding protein B (S100B).

Additional markers will comprise adiponectin, leptin, resistin, vascular cell adhesion molecule 1 (VCAM-1), von Willebrand factor (vWF), and osteoprotegerin (OPG). The analysis will also include neuron-specific enolase (NSE), intercellular adhesion molecule 1 (ICAM-1), furin, soluble CD25 (sCD25), sCD163, sCD14, myeloperoxidase (MPO), and cortisol. Collectively, these biomarkers are expected to provide valuable insights into the effects of psilocybin's broader impact on immune function, inflammatory pathways, and metabolic regulation.

Analysis strategy

Firstly, we intend to summarise essential participant characteristics and scrutinise outcome variables at both time points using descriptive statistics. We will then employ a linear mixed effects model (or equivalent) to assess the impact of 10 mg of psilocybin on Y-BOCS and MADRS scores, allowing us to determine the interaction between time and dose. Alternatively, paired t-tests (or equivalents) will be used to discern mean differences for other outcomes including the ID-ED task, reversal learning task, and information-seeking task. Tests for normality, homoscedasticity, and sphericity (where required) will be performed. We will ascertain effect size (Cohen’s d) and statistical power to gain a more nuanced understanding of the observed differences appropriate for our sample size of 20 completers. Furthermore, we will perform correlation analysis, exploratory factor analysis, and subgroup analyses based on participant characteristics to enrich our interpretations of outcomes. It will be necessary to adjust for baseline covariates and sensitivity analyses. GraphPad Prism, Python, R and MATLAB will be used to carry out the statistical analyses described and to produce appropriate figures such as line plots, scatter plots, and box plots. See Table 4 below for the time points of interest and the statistical plan.

**Table 4 TAB4:** Statistical plan for the main PsilOCD outcomes The purpose of this table is to maintain clarity and transparency regarding the main study outcomes. Additional analyses may be conducted in an exploratory fashion. Paired t-tests and ANOVA assume certain conditions such as normality, homoscedasticity, and, in the case of ANOVA with repeated measures, sphericity. All datasets will undergo testing, and if these assumptions are not met, suitable alternative tests will be employed (for instance, utilising the Welch t-test in place of the standard paired t-test). *First dosing day; **second dosing day. ID: Intradimensional; ED: Extradimensional; CANTAB: Cambridge Neuropsychological Test Automated Battery; LTP: Long-term potentiation; EEG: Electroencephalography; MMN: Mismatch negativity; ANOVA: Analysis of variance; Y-BOCS: Yale-Brown Obsessive Compulsive Scale; MADRS: Montgomery-Asberg Depression Rating Scale; BDNF: Brain-derived neurotrophic factor

Measure	Timepoints for Analysis
Primary Outcome Measures	
ID-ED Set-Shifting Task (CANTAB)	Two days- post 1 mg vs two days post 10 mg (paired t-tests or equivalent)
Plasticity via LTP Paradigm (EEG)	Screening vs 1 mg vs 10 mg (ANOVAs + paired t-tests or equivalent)
Predictive Processing via MMN (EEG)	Screening vs 1 mg vs 10 mg (ANOVAs + paired t-tests or equivalent)
Secondary Outcome Measures	
Reversal Learning Task (CANTAB)	Two days post DD1* vs two days post DD2** (paired t-tests or equivalent)
Paired-Associates Control Task (CANTAB)	Two days post DD1 vs Two days post DD2 (paired t-tests or equivalent)
Information-Seeking Task	One day post DD1 vs One day post DD2 (paired t-tests or equivalent)
Y-BOCS and MADRS	Linear mixed effects model (or equivalent) to test the interaction effect between time and dose (1 mg vs 10 mg) on Y-BOCS and MADRS scores.
Bloods: Plasma BDNF and Immune Factor Levels	DD1 vs DD2 (paired t-tests or equivalent)
Acute Measures (Self-Reported)	DD1 vs DD2 (paired t-tests or equivalent)
Self-Reported Well-Being and Affective Measures	Linear mixed effects model (or equivalent) to test the interaction effect between time and dose (1 mg vs 10 mg) on questionnaire scores.

Investigational medicinal product management

A Schedule 1 licence for the possession and storage of psilocybin has been obtained from the UK Home Office. Psilocybin will be supplied by COMPASS Pathways Ltd. Manufacture and encapsulation will be performed by Lonza Pharma and Biotech. Good Manufacturing Practice (GMP) will be maintained at all stages of manufacture. The investigational medicinal product (IMP) will be stored in a secure safe at Imperial College London, Hammersmith Campus.

Data management

Data will be managed as per the Imperial College Data Management Standard Operating Procedures and a study-specific data management plan. All data collection and management software has met the General Data Protection Regulation (GDPR) standards and has been approved by Imperial College London.

Dissemination

The findings of this study will be published in academic journals and shared across both academic and public platforms, including scientific conferences and public engagement forums in the media. Patient confidentiality will be upheld in all instances. All study-related publications and presentations will be managed by the Principal Investigator and Chief Investigator.

Ethics and trial registration

This study has received a favourable opinion from the London Central Research Ethics Committee (REC) (registration number: 21/LO/0804) and is sponsored by Imperial College London’s Research Governance and Integrity Team. All participants will provide their written informed consent to be screened and, if relevant, participate in this study. The Medicines and Healthcare Products Regulatory Agency (MHRA) has confirmed its status as a non-clinical trial and waived the need for MHRA approval. The study has been reviewed and approved by the Health Research Authority (HRA). The study protocol has undergone external peer review and was co-developed with patient advisors. All study staff have undergone Good Clinical Practice (GCP) training. The study has been adopted by the National Institute of Health Research (NIHR) Clinical Research Network (CRN) and has been registered on clinicaltrials.gov (NCT06258031). All in-person study sessions will take place at the CIPPRes Clinic, a centre founded by Imperial College London and CNWL.

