## Abstract

Background: Obsessive-compulsive disorder (OCD) is a complex condition marked by persistent distressing thoughts and repetitive behaviours. Despite its prevalence, the mechanisms behind OCD remain elusive, and current treatments are limited. This protocol outlines an investigative study for individuals with OCD, exploring the potential of psilocybin to improve key components of cognition implicated in the disorder. The PsilOCD study strives to assess the effects of low-moderate psilocybin treatment (10 mg) alongside non-interventional therapy on several facets of OCD. The main focus points of PsilOCD are cognitive flexibility, measured with cognitive tests, and neuroplasticity, assessed through electroencephalography (EEG).

Methods: 20 blinded participants with OCD will complete two dosing sessions, separated by four weeks, where they will receive 1 mg of psilocybin on the first and 10 mg on the second. The first dose serves as an active placebo, and the latter is a low-moderate dose that induces relatively mild-moderate emotional and perceptual effects. Participants will be supported by trained psychedelic therapists, who will sit with them during each dosing session and provide virtual preparation and integration sessions over the 12-week study period. Therapeutic support will be the same for both the 1 mg and 10 mg sessions. PsilOCD’s primary outcomes include scores in the intradimensional-extradimensional (ID-ED) shift task, which is an established measure of cognitive flexibility, and neuroplasticity as quantified by a visual long-term potentiation (vLTP) task. This task is delivered as part of an EEG paradigm and measures acute quantified changes in neuroplasticity in the brain’s visual system. The ID-ED task will be conducted twice, two days after each dosing session, and the EEG recordings will also be taken twice, immediately after each session. Secondary outcome assessments will include OCD and affective symptom severity, as well as an array of patient-reported outcome measures (PROMs), in the form of questionnaires designed to assess well-being, dissociable and well-established mood-related (affective) measures, and participants’ subjective experience of the psilocybin experience.

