In the most recent study by Moreno et al., participants saw a notable drop in their Y-BOCS scores, and adverse reactions or heightened anxiety related to the psilocybin were not reported. These findings suggest that the therapeutic potential of low doses of psilocybin for OCD may be linked to activating the 5-HT2A receptor within the relevant brain circuitry. Notably, the three highest doses all yielded significant improvements, implying that a low dose of psilocybin (10 mg, comparable to the lower 0.1 and 0.2 mg/kg doses administered by Moreno et al.) may be a viable treatment [54]. This is useful to determine, since many OCD patients fear loss of control and may be opposed to having a more intense psychedelic experience. Most studies assessing psilocybin in the context of mental health have explored 25 mg doses [48,58]. However, if meaningful improvements in OCD symptoms can arise from the administration of 10 mg, this may be preferable to many patients.

Literature suggests that 1 mg of psilocybin serves as a good control, or active placebo [40,42,48]. This dose falls at the lower limit of what is typically regarded as a 'microdose', and does not produce noticeable physiological, perceptual, or emotional effects [43,59]. Importantly, opting for a 1 mg dose rather than an inert placebo also enables better blinding, as all patients can be told that they will be given ‘up to 10 mg’ of psilocybin during each session. This decreases the chance of a ‘disappointment effect’ from the 1 mg dose, mitigating the risk of participants believing that they have been given no psilocybin during the first dosing session and responding emotionally. Participants should be given the same therapeutic support before, after, and during both dosing days.

How psilocybin might improve the nuanced, dissociable cognitive deficits of OCD

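### The primary vLTP recording is given two irreconcilable times, one inside and one after the stated period of drug effect

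*Protocol article*

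**What the plan says.** All references are to the protocol article.

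- *Mechanistic neurophysiology outcome measures*: vLTP is run three times, at screening and once on each dosing day. The dosing-day runs take place "after the effects of the drug have worn off (two hours after dosing").
- *Table 2*, primary neuroimaging hypothesis: "Participants will demonstrate higher capacity for neural plasticity two hours post 10 mg dose compared to the 1 mg dose".
- *Dosing Day 1 and 2*: "One hour after the substance wears off, the EEG vLTP paradigm will be carried out to quantify enhancements in plasticity".
- *Low-moderate dose psilocybin administration with psychotherapeutic support*: "drug effects expected to last between four and six hours". The same section adds, without naming vLTP, that "EEG recordings will be conducted both before and during the peak drug phase".
- *Abstract*: "the EEG recordings will also be taken twice, immediately after each session". *Overview and aims* likewise places the EEG directly after the psychedelic state.
- *Introduction*, on the 1 mg active placebo: this dose "does not produce noticeable physiological, perceptual, or emotional effects".

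Table 3 marks vLTP with one plain X per dosing day, although its legend has before/after codes that other measures use. Table 4 compares screening, 1 mg and 10 mg, with no clock time.

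**The concern.** The clause in the neurophysiology section contradicts the stated duration of effect. Two hours after dosing cannot also be after wear-off if effects last four to six hours. The dosing-day section then gives a different rule, and it names vLTP explicitly.

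The choice of time decides what the endpoint means. vLTP is built on visually evoked occipital responses, and the Introduction says psilocybin alters sensory perception. At two hours, a 10 mg recording made under drug effect would be compared with a 1 mg recording made with no noticeable effect. A difference could then reflect acute perceptual or arousal change and not the plasticity that the hypothesis claims. One hour after wear-off, the same contrast is post-acute. These are different quantities, and a reader could not check afterwards which one was prespecified.

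A secondary worry is the wear-off anchor itself. If 1 mg has no noticeable effect, one hour after wear-off has no obvious clock time on the first dosing day. Dose order is fixed (1 mg, then 10 mg), so the design does not balance out any resulting difference in time since dosing or time of day.

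**Working it through.** No sample-size or power figure is involved. The check is clock arithmetic on the article's own times, counted from dosing (hour 0).

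**Inputs**
- Duration of effect: D = 4 to 6 h (psilocybin administration section).
- Rule A: vLTP at 2 h (neurophysiology section and Table 2).
- Rule B: vLTP at D + 1 h (dosing-day section).

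**Step 1. Can Rule A be after wear-off, as stated?** Wear-off is at D = 4 to 6 h. Rule A precedes it by D − 2 = 4 − 2 to 6 − 2, which is 2 to 4 h. The statement is not reproduced: the two-hour time lies wholly inside the period of effect.

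**Step 2. Where does Rule B fall?** D + 1 = 4 + 1 to 6 + 1, which is 5 to 7 h post-dose.

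**Step 3. Gap between the rules.** (D + 1) − 2 = 5 − 2 to 7 − 2, which is 3 to 5 h, with the two times on opposite sides of wear-off.

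**Step 4. Does a charitable reading of Rule A help?** Suppose it meant two hours after effects end. That gives D + 2 = 6 to 8 h. The time is now post-acute but still 1 h later than Rule B, and it contradicts Table 2, which says two hours after the dose.

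**Step 5. Do other statements settle it?**

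| Source | Implied time | Relative to wear-off |
|---|---|---|
| Neurophysiology section (number), Table 2 | 2 h | during effects |
| Neurophysiology section (main clause) | after 4 to 6 h | after |
| Dosing Day 1 and 2 | 5 to 7 h | after |
| Abstract, Overview and aims | about 4 to 6 h, assuming the session ends at wear-off | after |
| Tables 3 and 4 | no time given | silent |

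The visit lasts about nine hours and ends at about 17:30, so arrival is near 08:30 (17:30 − 9 h). The dosing hour is not given, and the visit can accommodate either rule, so its length does not decide between them.

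**The case against.** The strongest reply is that the intent is recognisable. The dosing-day section, the Abstract, the Overview and the main clause of the neurophysiology section all point to a post-acute recording. Only a parenthesis and the hypothesis wording in Table 2 say otherwise. The *Bloods* section times samples at two hours after the end of the dosing session, so the two-hour figure may be loose shorthand for that. This is a fair guide to intent, but it does not rescue the text. Table 2 counts two hours from the dose, and the shorthand reading still misses the dosing-day rule by an hour.

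Two stronger readings are tempting, and the document does not support them.

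- A reader might count four or more incompatible vLTP timings, including one at the peak. The sentence about EEG before and during the peak does not name vLTP. A pair of recordings per dosing day also does not fit the single dosing-day vLTP run stated elsewhere. It may describe the resting-state or mismatch negativity recordings listed in Table 3. The Abstract and Overview agree with the dosing-day section to within about an hour. The material conflict is two-way.
- A reader might conclude that time since dosing will differ between the 1 mg and 10 mg days. The article does not say how wear-off is judged, and it gives both days one description and one approximate finishing time. A difference is a possible consequence of the wear-off anchor, not a stated feature.

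It is also true that exact windows commonly sit in a full protocol or EEG manual. Their absence is not the complaint here. The complaint is that the times which are stated contradict each other.

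**Conclusion.** Wrong as written. Two stated times for a primary outcome differ by 3 to 5 hours and place the 10 mg recording on opposite sides of wear-off. Following the two-hour time would record it under drug effect, while following the dosing-day section would record it afterwards. The conclusion rests on the article's own four-to-six-hour duration and on the three places that name vLTP or state its hypothesis (the neurophysiology section, Table 2 and the dosing-day section). It does not depend on the peak-phase sentence or on the Abstract.

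The possible confounding of dose with time since dosing is a secondary inference from the 1 mg dose having no noticeable effect. It supports a common clock offset but is not itself an error in the text. Nothing here shows that recordings will in fact be made under acute effect, only that the article permits that reading.

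**What to change.** - State one nominal vLTP time since dosing that is consistent with the post-acute intent and with the stated duration of effect. To be post-acute across the whole stated range, it must fall later than six hours after dosing.
- Apply the same clock offset and the same window on both dosing days.
- Bring the neurophysiology section, Table 2 and the dosing-day section into line with it, and align the wording of the Abstract and the Overview.
- Log the actual vLTP start time for each participant and day.
- In the psilocybin administration section, state which EEG measures are recorded before and during the peak, and that they are separate from the primary vLTP recording.

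**Cost.** Wording in a handful of places and one logged time per recording, with no added visit or recording. The downside is small: at a fixed offset T, time since individual wear-off ranges from T − 6 to T − 4 h, a spread of 2 h between participants. In return, time since dosing is the same for both doses, which is what the paired comparison needs.
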